#### Range of motion

The measurement of *shoulder range of motion* will be performed by using a universal goniometer according to standardized procedures 
[39]. Active and passive shoulder movements will be measured and include the measurements of forward flexion, abduction, internal rotation, external rotation and horizontal abduction movements.

#### Arm function

*Arm function* will be assessed using the Disabilities of the Arm, Shoulder and Hand scale (DASH) 
[40]. The scale measures the effect of arm function on 30 different daily activities. It also examines symptoms such as pain, weakness and numbness, and the degree of disability related to work and recreational activity. The scale is scored from 0 to 100 with higher scores indicating greater disability. This scale has been well documented and shown to be reliable and valid.

#### Peripheral neuropathy

Peripheral neuropathy will be assessed by self-report and objective measures of sensorimotor function, strength and balance testing.

### Blood data collection

The baseline blood draw will be done after an overnight fast of at least eight hours. A 60 ml sample will be taken at baseline and a 30 ml sample will be taken at 1 and 3 year follow-ups. For this study, we will store 24 aliquots per person for baseline blood draw (14 serum, 6 plasma, 2 buffy coat and 2 red blood cells) and 16 aliquots per person for 1 and 3 year follow-up blood draw (8 serum, 5 plasma, 1 buffy coat and 2 red blood cells). A complete blood collection, processing, shipping and storage protocol has been developed to ensure standardization of the procedures for the bloods at the collection sites in Calgary (Calgary Laboratory Services) and Edmonton (Cross Cancer Institute). The aliquoted blood samples will be stored in our −86°C freezers.

### Medical record abstraction

Health Record Technicians from the Alberta Cancer Registry will use standardized forms and methods to abstract the medical charts for all of the participants at regular intervals during the cohort study. The form was previously developed and tested for our past PA and breast cancer cohort study that evolved from a population-based case–control study that we conducted in Alberta 
[41]. Medical variables to be abstracted will include pathologic and clinical disease stage (TNM), type of surgery, and all treatment and follow-up care including data on chemotherapy, radiation therapy, and hormone therapy. Pathology data will include tumor size, grade, histology, estrogen receptor status, human epidermal growth factor receptor 2 (HER2-neu) status, type and results of computerized tomography (CT) or positron emission tomography (PET) scans, status of margins (with breast conserving surgery), and pathology of lymph nodes (if surgically sampled).

*Treatment completion rates* will be estimated for chemotherapy and hormone therapy but not for radiation therapy since few survivors fail to complete radiation therapy. For chemotherapy completion rate, we will estimate the average relative dose intensity (RDI) received for the originally planned regimen based on standard formulae as we have done in a previous RCT 
[42]. For hormone therapy completion rate, it is not feasible to obtain an objective measure of treatment adherence. Consequently, participants will be asked to report if they have stopped taking their prescribed hormone therapy at any time before its intended completion and the reasons for stopping their treatments.

*Disease endpoints* will be defined and assessed based on the Standardized Definitions for Efficacy End Points in Adjuvant Breast Cancer Trials (the STEEP system) 
[43]. We selected recurrence-free interval (RFI) as our primary disease endpoint because it consists of events directly attributed to breast cancer including invasive ipsilateral breast tumor recurrence, local/regional invasive recurrence, distant recurrence, and death from breast cancer. We will also examine other composite disease endpoints as secondary endpoints including overall survival, invasive disease-free survival, distant disease-free survival, distant relapse-free survival, breast cancer-free interval, and distant recurrence-free interval. Finally, we will examine the single disease endpoints of death from breast cancer and death from non-breast cancer. These endpoints will be abstracted by the health records technicians at the time of the medical chart reviews described above.

Information on all deaths that occurred in the province is provided by Vital Statistics Alberta (VSA) to the ACR on a monthly basis with underlying cause of death provided by Statistics Canada to VSA. There is an average three-month time lag between the actual death occurrence and reporting to the ACR. For cases that leave the province after diagnosis, several mechanisms exist to capture their deaths with reciprocal agreements between other provinces and record linkages with the Canadian Mortality Database that are undertaken with the ACR data. These agreements and processes ensure that vital status can be determined for over 95% of cases. For cases who have left the province and who are not known to be dead, the date of leaving Alberta will be used as the censoring time. For the follow-up of this cohort, yearly checks of the vital status of the breast cancer survivors will be conducted through linkages with the ACR. Cause of death and date of death will be obtained from this source.

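### Women who leave Alberta are censored at departure only if not known to have died, so their follow-up time depends on the outcome; the effect is modest for RFI and larger for death endpoints.

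*Protocol article*

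**What the plan says.** The rule is in the vital-status paragraph of the Protocol article, Methods, Medical record abstraction.

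- Deaths outside Alberta are sought: "For cases that leave the province after diagnosis, several mechanisms exist to capture their deaths with reciprocal agreements between other provinces", and also through "record linkages with the Canadian Mortality Database that are undertaken with the ACR data".
- On completeness: "These agreements and processes ensure that vital status can be determined for over 95% of cases".
- The censoring rule is limited to one group of leavers, those "who are not known to be dead, the date of leaving Alberta will be used as the censoring time".
- Vital status is checked yearly through the Alberta Cancer Registry (ACR), and "Cause of death and date of death will be obtained from this source".

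The same section defines the primary endpoint, RFI, as a composite of invasive ipsilateral recurrence plus "local/regional invasive recurrence, distant recurrence, and death from breast cancer". On the source of the endpoint data it says: "These endpoints will be abstracted by the health records technicians at the time of the medical chart reviews described above". The mechanisms described for women outside the province concern deaths only.

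**The concern.** A censoring time should be fixed without reference to what happens afterwards. Here two women who leave on the same day are handled differently according to their later fate. If one dies and the death is found, her follow-up runs to death and she contributes an event. If the other stays alive, her follow-up is cut back to the day she left. Deaths after departure enter the numerator, and the matching event-free time is removed from the denominator.

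Two consequences follow. Event rates per person-time are too high among movers. If the tendency to leave differs by fitness, the inflation differs between the groups being compared and the HR is biased: towards or past 1 if fitter women leave more often, away from 1 if less fit women do. More events or a larger cohort would not remove this bias.

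The endpoints are not equally exposed. For overall survival and cause-specific death, every captured death after departure enters. For RFI, only breast cancer deaths enter, because no capture of recurrences outside the province is described.

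**Working it through.** **The plan's own figure on loss.** Sample size and power considerations gives 460 events and a 10% loss to follow-up: 460 × (1 − 0.10) = 414, which reproduces. The article does not say how much of that 10% is out-migration, so the departure rate has to be assumed.

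**Inputs from the article.** HR 0.70; a 20% five-year recurrence rate, equivalent to a constant hazard of −ln(0.80)/5 = 0.0446 per year; median follow-up of about seven years; 414 expected events.

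**Assumptions.** Two equal fitness groups, with hazard 0.0446 per year in the less fit group; follow-up uniform on 4.5 to 9.5 years; exponential departure with 5, 10 or 15% leaving by year 7; hazard of breast cancer death after recurrence 0.25 per year, varied from 0.1 to 0.4.

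**Hand check of the rate inflation.** With departure hazard m = −ln(1 − p)/7, the share of a seven-year follow-up falling after departure is about m × 7/2 = −ln(1 − p)/2:

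- p = 5%: 0.0513/2 = 2.6%
- p = 10%: 0.1054/2 = 5.3%
- p = 15%: 0.1625/2 = 8.1%

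Nearly all of this is survivors' time, which the rule discards. The inflation should therefore be slightly below these values where every later event is captured.

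**Simulation.** The stated rule is compared with censoring every leaver at departure, using an unadjusted Cox model. The death-endpoint column counts every event after departure, at the same hazard for illustration. The RFI column counts only breast cancer deaths after departure.

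| Scenario | Death endpoints | RFI |
|---|---|---|
| Rate inflation, 5/10/15% leave | about 2/5/7% | about 1/2/3% (0.25 per year) |
| HR, true 0.70, leaving unrelated to fitness | about 0.70 | about 0.70 |
| HR, true 0.70, 15% of fit and 5% of unfit leave | about 0.74 | 0.71-0.72 (0.1-0.4 per year) |
| HR, true 0.70, reversed | about 0.67 | 0.68-0.69 (0.1-0.4 per year) |

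Censoring every leaver at departure returns about 0.70 in every scenario.

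**Second check with separate death processes.** Here the RFI hazard is −ln(1 − 460/1500)/7 = 0.0523 per year, non-breast-cancer death is 0.01 per year, and 95% of deaths after departure are captured. With about 5, 9 and 17% leaving, unrelated to fitness, the RFI rate rises by about 1, 2 and 3% over complete follow-up, and the all-cause death rate by about 2, 4 and 9%. If fitter women leave two to three times as often, a null HR becomes about 1.02-1.03 for RFI and 1.04-1.08 for overall survival. If less fit women leave three times as often, it becomes about 0.975 and 0.94.

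**Scale against sampling error for RFI.** If 414 events are spread evenly over quartiles, the top-versus-bottom contrast rests on about 207, so SE(log HR) ≈ √(4/207) = 0.139. The RFI shifts are ln(0.72/0.70) = 0.028 and ln(0.68/0.70) = −0.029 at the outer ends, about a fifth of one SE.

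**Events given up.** Censoring every leaver at departure for RFI drops the breast cancer deaths found afterwards: about 4 to 14 of 414 for 5 to 15% leaving, at 0.25 per year.

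**The case against.** The strongest case against is about size. A reader might infer that the primary RFI hazard ratio could move to 0.74 or 0.67. The article does not support that: those values require every event after departure to be captured, recurrences included, and it describes capture of deaths only. The RFI shift is small against its standard error, and it needs a threefold difference in departure between fitness groups, for which the article offers no evidence. The planned adjustment for age, BMI, stage, treatment and co-morbidity would remove part of any such difference, and the simulations are unadjusted. Overall survival and the death endpoints, where the effect is larger, are not the primary endpoint. All of this stands, and it limits the severity.

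A second objection is that the article never states that a death after departure counts as an event at its date; the sentence sits in a paragraph on vital status, and endpoint-specific censoring may be set out elsewhere. It is fair to call that step inferred. But the restriction to women not known to have died would serve no purpose if every leaver were censored at departure. What is printed is an explicit censoring rule, not a missing detail.

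A third point concerns the remedy. A reader might take the figure of over 95% as completeness among leavers. It is stated for all cases. If 5 to 15% leave, it is compatible with poor ascertainment among those who left, and no capture is described for women who leave Canada. Following all leavers to the linkage date would count unmatched deaths as survival, a bias in the opposite direction. This stands and is why a sensitivity analysis is needed.

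**Conclusion.** The defect holds: as written, the end of follow-up for women who leave Alberta depends on whether they are known to have died. It inflates rates per person-time and biases the HR only if leaving is related to fitness.

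For the primary RFI endpoint the effect is modest. It matters more for overall survival and cause-specific death, which the article names among the disease outcomes of its first project. The sizes rest on assumed departure rates, an assumed hazard of death after recurrence, and the inference that deaths after departure are counted at the death date. The article does not support reading this as a flaw that invalidates the primary analysis. It should be fixed because the rule is wrong in principle and cheap to correct.

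**What to change.** Replace the sentence with one rule per endpoint that does not look at the outcome.

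- **RFI and the other recurrence endpoints:** censor every leaver at the date of leaving Alberta and disregard later deaths. This costs about 4 to 14 of 414 events under the assumptions above.
- **Overall and cause-specific death:** either censor every leaver at departure, or follow every leaver to the common linkage date whether or not a death is found. Name one as the main rule and report the other as a sensitivity analysis, because completeness among leavers is not stated.

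This takes a few lines of text and no new data collection, since departure dates and yearly linkage are already planned. Reporting the number of leavers by fitness quartile would show whether the HR could have been affected.

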### Sample size and power considerations

Although a cohort study such as this one has many exposures, time points, and endpoints of interest, we chose to power our study using cardiorespiratory fitness at one-year follow-up as the primary exposure/time point, and recurrence free interval (RFI) as the primary endpoint because of the importance of these variables but also because of the substantial power needed to detect this association. By designing the study with adequate power for this association, we ensured sufficient power for all the other objectives that require substantially less power. We designed the study to detect a 30% risk reduction of RFI in survivors who are in the top quartile of cardiorespiratory fitness, compared to those who are in the lowest quartile (hazard ratio = 0.7). The sample size was determined under the framework of Cox proportional hazards (PH) models, adjusting for known potential confounders such as age, BMI, tumor stage, treatment, alcohol intake, diet, smoking and co-morbidity. A statistical power of 80% and a two-sided α = 0.05 were used. This setting requires 223 to 401 events (PASS 2005); the exact number depends on how strong the association is between cardiorespiratory fitness and the confounders in the Cox PH model. A stronger association requires a larger number of events. The association among variables is quantified by *R*^*2*^ of a multiple linear regression model where cardiorespiratory fitness is regressed onto the confounders. In the above calculation, we have considered a range of *R*^*2*^ between 0.1 (requiring 223 events) and 0.5 (requiring 401 events) that we deemed realistic. The *R*^*2*^ can be reduced by using cardiorespiratory fitness quartiles that are adjusted for some of the major confounders such as age and BMI, ensuring the *R*^*2*^ value of less or equal to 0.5. Thus, our study is sufficiently powered for the primary objective if we have more than 401 events.

The annual recurrence rate for localized invasive breast cancer is estimated to be 2 ~ 3% 
[44]. For stage I – IIIc patients combined, a first five-year recurrence rate of 20% has been reported 
[45,46]. To attain the desired number of events, we are using a stratified sampling design based on the projected breast cancer cases diagnosed in 2012–15 who will be treated in Edmonton or Calgary. We plan to recruit a total of 1500 breast cancer survivors from the two locations. Given the projected numbers of survivors seen at two locations for each stage, and, assuming an overall 50% consent rate for participation, the recruitment will be completed within 5 years. This recruitment plan will provide a median of about seven years of follow-up by the end of this study in year 2022, and will yield a minimum of 460 events. Allowing for a 10% loss to follow-up, we expect to observe, at minimum, 414 events in this cohort.

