## Discussion

The primary focus of the AMBER Study will be to identify the independent and interactive associations of PA and HRF with disease outcomes (e.g., recurrence, breast cancer-specific mortality, overall survival). Other important health outcomes will include treatment completion rates, symptoms and side effects (e.g., pain, lymphedema, fatigue, cognitive dysfunction), and PROs (e.g., QoL, anxiety, depression, self-esteem, happiness). We will also be able to examine the mediators and moderators of any observed associations between PA, HRF, and health outcomes. Finally, we will be able to identify the key determinants of PA and HRF including demographic, medical, and social cognitive variables, at various time points across the survivorship trajectory. Taken together, these data will provide a detailed understanding of the unique benefits, risks, and determinants of PA and HRF at multiple time points of survivorship so that intervention strategies can be developed to help breast cancer survivors achieve and maintain healthy levels of PA and HRF. The AMBER Study is designed initially to address the following five major research themes.

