### Physical activity, health-related fitness, and disease outcomes

The primary aim of this project is to examine the associations between self-reported and objective PA (including sedentary behavior), HRF (including body composition), and disease outcomes in breast cancer survivors (including recurrence-free interval, breast cancer mortality, and overall survival). These data will provide critical information on the optimal type, volume, and pattern (i.e., how the volume is achieved over a given week) of PA that may be most strongly associated with disease outcomes in breast cancer survivors. Moreover, while previous studies have used self-report PA assessments, the use of accelerometers to measure PA will provide an accurate (and gold-standard) estimate of PA at multiple time points across the survivorship trajectory. Further, no studies have examined associations between objectively-determined PA and disease endpoints. Multivariable analyses will be able to determine any independent associations of the PA and HRF variables with disease outcomes that may identify one or more PA-related exposures of primary importance. For example, two research questions will be to determine whether: (a) cardiorespiratory fitness and muscular strength or other HRF assessments are independently associated with disease outcomes among breast cancer survivors, and (b) vigorous PA and sedentary behavior are independently associated with disease outcomes. A secondary aim is to examine potential moderators (effect modifiers) of the associations between PA, HRF, and disease outcomes. These data will provide critical information on which subgroups of survivors may benefit the most from engaging in PA and may also even identify different optimal PA prescriptions for different survivor subgroups. The ultimate goal of this project is to provide insights regarding the relative importance of various aspects of the PA prescription and the various HRF components for breast cancer outcomes that will be directly relevant for PA and sedentary behavior recommendations for breast cancer survivors.

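### Powering the study for fitness and recurrence-free interval does not assure power for narrower disease endpoints or for interaction and moderator aims, so the general power claim is too broad

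*Protocol article*

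**What the plan says.** Under Sample size and power considerations, the article picks one-year cardiorespiratory fitness as primary exposure and RFI as primary endpoint, partly because this association needs a great deal of power. It concludes that by doing so "we ensured sufficient power for all the other objectives that require substantially less power". The target is a hazard ratio of 0.7 between the top and bottom fitness quartiles. "A statistical power of 80% and a two-sided α = 0.05 were used". The required number of events depends on the R² of fitness on the confounders, "between 0.1 (requiring 223 events) and 0.5 (requiring 401 events) that we deemed realistic". The study is expected to yield at least 460 events, or 414 after 10% loss to follow-up.

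Under Medical record abstraction, RFI is defined to include death from breast cancer. Distant recurrence-free interval is listed among the secondary endpoints, and the text adds: "Finally, we will examine the single disease endpoints of death from breast cancer and death from non-breast cancer". The Discussion says the primary focus is to "identify the independent and interactive associations of PA and HRF with disease outcomes", with breast cancer mortality among the examples. The disease-outcomes project states: "A secondary aim is to examine potential moderators (effect modifiers) of the associations between PA, HRF, and disease outcomes".

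**The concern.** The assurance rests on the idea that the powered association is the most demanding one. That is not so for two groups of stated objectives. An endpoint that is part of RFI cannot supply more events than RFI and will normally supply fewer. An interaction of a given size on the log hazard scale is estimated less precisely than a main effect of that size from the same events.

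At stake is how later results are read. A null result for breast cancer mortality, or for an interaction, could be taken as coming from an adequately powered analysis. Subgroup differences could be over-read too, because the disease-outcomes project hopes that moderator analyses might lead to different activity prescriptions for different subgroups.

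**Working it through.** **Inputs, all from the article.** Two-sided α = 0.05; power 80%; hazard ratio 0.7; 223 events required at R² = 0.1 and 401 at R² = 0.5; 460 × 0.9 = 414 events expected; 1500 women.

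**The plan's own figure.** The R² adjustment is consistent with itself: 223 × 0.9 = 200.7 and 401 × 0.5 = 200.5, so about 200.5 events before adjustment. The stated inputs do not reproduce that base. With the usual Cox formula and a 50/50 split, D = (1.960 + 0.842)² / [0.25 × (ln 0.7)²] = 246.8, giving 274 events at R² = 0.1 and 494 at R² = 0.5. That is a separate matter. The check below scales from the plan's own 223 and 401, which is the more favourable basis for the plan.

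**Scaling formula.** If D events give 80% power, then E events give power Φ[√(E/D) × 2.802 − 1.960] for the same hazard ratio.

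**1. RFI itself.** At 414 events, power is 97% (D = 223) or 81% (D = 401). The margin at R² = 0.5 is 414 − 401 = 13 events; 401/414 = 0.969.

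**2. Endpoints with fewer events than RFI.** Every woman who dies of breast cancer has had an RFI event, so breast cancer deaths cannot outnumber RFI events. The article does not list the components of distant recurrence-free interval, but by its name it leaves out local and regional recurrence. No event counts are given for either, so the table shows a range, at hazard ratio 0.7.

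| Share of RFI events | Events | Power, R² = 0.1 | Power, R² = 0.5 |
|---|---|---|---|
| 90% | 373 | 95% | 77% |
| 70% | 290 | 89% | 66% |
| 50% | 207 | 77% | 52% |
| 30% | 124 | 55% | 34% |

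At R² = 0.5, any share below about 97% falls short of 80%. At R² = 0.1 the limit is 223/414 = 54%.

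**3. Interaction with a binary moderator.** If a share q of the events lies in one moderator group, the variance of the difference in log hazard ratios is 1/[q(1 − q)] times that of the main effect. At q = 0.5 the factor is 4. For an interaction as large as the main effect (ratio of hazard ratios 0.7):

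- Events for 80% power: 4 × 223 = 892 (R² = 0.1) to 4 × 401 = 1604 (R² = 0.5). The latter exceeds the 1500 women enrolled.
- Power at 414 events: Φ[√(414/892) × 2.802 − 1.960] = 48%; Φ[√(414/1604) × 2.802 − 1.960] = 30%.
- Ratio of hazard ratios detectable with 80% power at 414 events: 0.59 (R² = 0.1) to 0.50 (R² = 0.5).

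An unbalanced moderator is worse: the factor is 4.8 at q = 0.3 and 6.25 at q = 0.2. On the 274 and 494 basis, the balanced case needs 1097 to 1974 events, and power at 414 is 41% to 25%.

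**The case against.** The clause can be read restrictively, as covering only those objectives that do need less power. It would then be true but empty. The sentence before it, which justifies the choice by the large power that this association needs, shows that a general assurance is meant.

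The sentence is also reasonable for much of the programme. Patient-reported, functional, biomarker and determinant objectives largely use continuous measures in up to 1500 women. Among the disease endpoints, invasive disease-free survival and breast cancer-free interval are broader than RFI and need not have fewer events. This stands, and it is why the sentence should be narrowed and not removed.

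The other disease endpoints are secondary, the moderator language is tentative, and no test or decision rule depends on the sentence. This also stands and limits the consequence. Nor is it a fault that an article gives no power for each secondary endpoint. The fault is a positive claim that the stated aims do not bear out.

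Three stronger readings are tempting but unsupported:

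- A reader might turn the Background's 88% five-year relative survival into a count of breast cancer deaths and conclude that even 223 would not be reached. That figure is for Canadian breast cancer overall. The cohort leaves out metastatic disease, but also node-negative tumours below T1c, and it samples by stage to gain events, so the direction of the difference is unknown. The 10% loss may also not apply to deaths, since vital status is said to be obtainable for over 95% of cases.
- A reader might infer that deaths from other causes must be rarer than RFI events. The article gives no age distribution or other-cause mortality to show it.
- A reader might take the factor of four as general. It holds for a balanced binary moderator and an interaction as large as the main effect. Activity and fitness are graded exposures, so for their interaction it is only a benchmark.

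**Conclusion.** The claim of sufficient power for all other objectives does not hold. Breast cancer death and distant recurrence-free interval are not assured 80% power at hazard ratio 0.7: the allowance at R² = 0.5 is only about 3% of the RFI events. If R² is near 0.1, an endpoint with at least 223 events does keep 80%, and a stronger effect than 0.7 would need fewer events. Interaction and moderator analyses of disease outcomes fall well short under the balanced, equal-size assumption. With a balanced moderator, 414 events suffice only if the interaction log hazard ratio is about 1.5 (R² = 0.1) to 2 (R² = 0.5) times the main effect. A smaller interaction or an unbalanced moderator needs more events.

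The conclusion rests on the plan's own event requirements, its expected 414 events, and the definition of RFI; for distant recurrence-free interval it rests on the name. The primary fitness-RFI analysis is not affected by this point. The correction is worth making because the assurance covers breast cancer mortality and interactions, both of which the article places in its primary focus.

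**What to change.** In Sample size and power considerations:

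- Restrict the assurance to the continuous and patient-reported outcome objectives.
- State that, among disease outcomes, power was set only for the main effect of one-year cardiorespiratory fitness on RFI.
- State that breast cancer death, distant recurrence-free interval, and the interaction and moderator analyses of disease outcomes are not assured 80% power, and will be reported as exploratory estimates with confidence intervals.

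The change is to wording only. Design, sample size and data collection stay as they are; the cost is a less favourable power statement.

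### The stated 223 to 401 events do not follow from the stated inputs; at 414 events the top-versus-lowest-quartile contrast has about 68% to 44% power, not 80%

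*Protocol article*

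**What the plan says.** All the inputs are in the Protocol article, section Sample size and power considerations. The effect is set for "survivors who are in the top quartile of cardiorespiratory fitness, compared to those who are in the lowest quartile (hazard ratio = 0.7"). The error rates follow: "A statistical power of 80% and a two-sided α = 0.05 were used". The method is a covariate-adjusted Cox model: "The sample size was determined under the framework of Cox proportional hazards (PH) models, adjusting for known potential confounders". The result is given as "This setting requires 223 to 401 events (PASS 2005"). R² comes from regressing fitness on the confounders and is taken to lie between 0.1 (223 events) and 0.5 (401 events). The upper figure becomes the decision rule: "Thus, our study is sufficiently powered for the primary objective if we have more than 401 events".

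The same section then projects at least 460 events in a cohort of 1500, or 414 after 10% loss to follow-up, so the rule appears to be met. It also relies on this calculation to claim adequate power for the study's other objectives.

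**The concern.** The required number of events in a Cox model depends on the hazard ratio, the error rates, R² and the variance of the exposure. The first three are stated, and the contrast described puts a ceiling on the fourth. The stated event counts are too small for that ceiling.

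There is a second problem. A comparison of the top quarter with the bottom quarter draws its information from events in those two quarters only, but the 414 expected events are counted over the whole cohort.

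At stake is the power claim for the primary exposure and primary endpoint. If 401 is not the right threshold, clearing it with 414 does not show that the study is adequately powered.

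**Working it through.** **Inputs** (all from the section cited): HR 0.7, so (ln 0.7)² = 0.1272; two-sided alpha 0.05 and 80% power, so (1.960 + 0.842)² = 7.849; R² = 0.1 or 0.5; 414 expected events.

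**Formula:** D = (z_α/2 + z_β)² / [var(X) · (ln HR)² · (1 − R²)]. Here 7.849 / 0.1272 = 61.7, so D = 61.7 / [var(X)(1 − R²)].

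**Step 1: try to reproduce the plan's figures.** The R² step is consistent: 223 × 0.9 = 200.7 and 401 × 0.5 = 200.5. The unadjusted base of about 200.6 events is where the difficulty lies. It implies var(X) = 61.7 / (0.9 × 223) = 0.307 and 61.7 / (0.5 × 401) = 0.308, an SD of about 0.555. A 0/1 exposure has variance p(1 − p), which is at most 0.25 (SD 0.5).

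**Step 2: the best possible two-group case.** With var(X) = 0.25 (whole cohort split evenly, every event informative), D = 61.7 / (0.25 × 0.9) = 274 and 61.7 / (0.25 × 0.5) = 494. At 401 events and R² = 0.5, power is Φ(√(401 × 0.25 × 0.5 × 0.1272) − 1.960) = Φ(0.565) = 71%.

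**Step 3: the stated contrast.** Assume the two extreme quartiles hold about half of all events, evenly divided. The effective variance per cohort event is then 0.5 × 0.25 = 0.125.
- Events needed: 61.7 / (0.125 × 0.9) = 548 and 61.7 / (0.125 × 0.5) = 987. With no confounder adjustment at all (R² = 0) it is 61.7 / 0.125 = 494, still more than 414.
- Power at 414 events: Φ(√(414 × 0.125 × 0.9 × 0.1272) − 1.960) = Φ(0.474) = 68%; with 0.5 in place of 0.9, Φ(−0.146) = 44%.
- Detectable HR at 414 events: exp(−√(7.849 / (414 × 0.125 × 0.9))) = 0.66; with 0.5 in place of 0.9, 0.58.
- If event rates fall across quartiles as 1, 0.9, 0.8, 0.7, power is 67% and 43%. Two Cox simulations gave 66–67% and 40–43%.

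**Step 4: other codings** (two-sided; each pair is R² = 0.1 / 0.5)

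| Exposure coding | var(X) | Events needed | Power at 414 |
|---|---|---|---|
| Stated in the plan | not given | 223 / 401 | 80% claimed above 401 |
| 50:50 split, all events | 0.25 | 274 / 494 | 93% / 73% |
| Normal, quartile medians | 1/2.301² | 363 / 653 | 85% / 61% |
| Top quartile vs rest | 0.1875 | 366 / 658 | 85% / 60% |
| Normal, quartile means | 1/2.542² | 443 / 797 | 77% / 52% |
| Trend over quartiles, scored 0 to 1 | 1.25/9 | 494 / 888 | 73% / 48% |
| Top vs lowest quartile | 0.125 | 548 / 987 | 68% / 44% |
| Normal, 75th vs 25th percentile | 1/1.349² | 125 / 225 | >99% / 97% |

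No row gives 223 / 401. Figures close to them appear only with a one-sided 5% test on two equal groups holding all the events (216 / 389 by the formula above; 221 / 397 by Freedman's), or with an unstated SD of about 0.55.

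**The case against.** The strongest reply is that the exposure's coding and SD are not stated. This is a condensed article citing a software run, and the SD may simply have been left out. R² is defined by a linear regression of fitness on the confounders, which suits a continuous or scored exposure, and for such an exposure a variance above 0.25 is possible. An SD of 0.555 would spread HR 0.7 over 1/0.555 = 1.80 SD of fitness, which lies between the interquartile distance (1.35 SD) and the distance between extreme-quartile means (2.54 SD).

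It can also be said that 44–68% is only one scenario, that 414 is a stated minimum, that 0.5 is the upper limit for R², and that several codings exceed 80% at R² = 0.1.

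Part of this stands. Exact power does depend on the coding, and the statement that power is below 80% throughout the R² range is specific to the top-versus-lowest contrast. Two things do not stand. First, 1.80 SD matches no natural quartile summary tried, and the text describes membership of two quartiles, not points on a continuous scale. Second, the 401-event rule is set at R² = 0.5, where every group, trend, quartile-mean or quartile-median coding gives 44–73% at 414 events. Only the percentile reading exceeds 80% there, and it does not yield 223 to 401 either.

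A further caution: what a null result would say about HR 0.7 depends on the observed confidence interval. Low planned power makes an inconclusive interval more likely; it does not settle the interpretation in advance.

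**Conclusion.** The point holds. The 223 to 401 events do not follow from the stated contrast, hazard ratio, power and two-sided alpha, because they need a variance of about 0.307 where a two-group contrast allows at most 0.25. Even on the most generous two-group reading, the 401-event rule gives 71% power.

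For the contrast as written, the requirement is about 548 to 987 cohort events, against 414 expected. These figures assume that the extreme quartiles hold about half of the events, roughly evenly divided; allowing for unequal rates changes power by only about one percentage point. The shortfall applies at every R² the article treats as realistic.

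This is a must-fix, since the figure is the stated criterion for adequate power on the primary objective and is extended to the other objectives.

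**What to change.** First state how fitness enters the primary Cox model (quartile indicators, trend score or continuous), the variance used, whether the calculation was one- or two-sided, and whether event counts refer to the cohort or to the two extreme quartiles. Then recalculate and do one of the following:

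- Replace the 223 to 401 range and the 401-event rule with the requirement for the contrast to be tested: about 548 to 987 cohort events for top versus lowest quartile, on the half-of-events assumption.
- Keep the 414 expected events and restate either the power (about 68% to 44%) or the hazard ratio detectable with 80% power (about 0.66 to 0.58).

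If the primary analysis will use a trend or continuous fitness, give the figures for that coding instead. The claim about the other objectives should be qualified to match.

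The cost is a rewritten power paragraph and a less favourable power statement. Recruitment and follow-up need not change.
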